## 5. Patient Inclusion

### ***5.1. Time plan for inclusion***

Patients will be screened for their eligibility after informed consent. Screening examinations may be distributed over three working days and should be performed in a time window of 30 to 2 days before treatment. There are no restrictions or recommendations with regard to the time after first diagnosis or the stage of the disease beyond the inclusion and exclusion criteria.

### ***5.2. Mode of assignment of patients to treatment***

Suitable patients in the patient data base of the Centre for Ophthalmology have already been identified and invited to an exploratory non-invasive trial, which has been running since December 2012 ("Detaillierte Genotyp-Phänotyp Analyse bei Patienten mit erblichen, genetisch gesicherten Netzhauterkrankungen" "Detailed genotype-phenotype analysis of patients with inherited genetically ensured retinal-diseases"). The patients out of this sample who qualify and are interested in participation in the rAAV.hCNGA3 trial will be invited for informed consent and screening visit.

## 6. Intervention

### 6.1. Treatment

See Appendix 1 for the rationale for vector and dosing for more details of the procedure. For reconstitution see detailed description in the Investigator Brochure.

1st: Standard three-port 23G pars plana vitrectomy (removal of vitreous humor and posterior hyaloid membrane) with balanced salt solution used to replace the vitreous humor and stabilize the eye during the procedure.

[figure not shown]

Figure 4: Scheme of injection

2nd: Balanced salt solution will be used to induce a shallow, localized primary retinal detachment involving the fovea (marked 'F' in Fig. 4) in an area of ca. 2mm diameter. The retinotomy (black dot) will be placed just central of the superior temporal branch of the central retinal artery (see Figure 4). This has given the most reproducible results in the non-human primate study with regard to localization of bleb formation.

3rd: Once the subretinal space has been pre-formed, 100 µl vector solution will be applied using a disposable 41G subretinal injection needle within a standard 23G body to fit the port system.

4th: An indentation search is performed gently to avoid vortexing of fluid inside the eye, which might induce a Venturi suction effect over the self-sealing retinotomy. Laser is applied to any peripheral breaks after relief of vitreous traction. Gas will be avoided where possible as it may induce a macular fold or displace subretinal vector to non-therapeutic regions. All vitrectomy ports will be sutured watertight at the end of surgery (e.g. using 8-0 vicryl sutures).

### 6.2. Concomitant medication

There are no forbidden medications during trial participation beyond the avoidance of anticoagulants around the surgical intervention with time lags depending on the half-life of the relevant drugs. Any concomitant medication will be documented during the trial.

## 7. Endpoints for Safety and Efficacy of a single subretinal injection of rAAV.hCNGA3 genome

### 7.1. Efficacy

Efficacy data (improvement in visual function) and patient reported outcomes will be investigated exploratively as well as retinal imaging. They are all secondary endpoints in this trial.

15. BCVA assessed using the ETDRS visual acuity protocol
16. Contrast sensitivity
17. Anomaloscopy
18. Cambridge Colour test
19. Flicker Fusion Test
20. Colour Constancy
21. MP-1 Microperimetry (20°)
22. Dark adaptation test (FST)
23. IR-Video-Pupillography
24. OCT, AO-SLO, IR, FAF and angiography recordings
25. FST (red/blue) and Ganzfeld-ERG
26. VFQ25
27. Brief Symptom Inventory (BSI)
28. A3-PRO (intervention-specific scale assessing patient reported outcome)

### 7.2. Safety

#### 7.2.1. Ocular and systemic safety

**Safety** as primary endpoint will be assessed by clinical examination of  
*Ocular safety*

3. loss of  $\geq 15$  letters visual acuity at 1m
4. severe, vector-induced, intraocular inflammation unresponsive to treatment

*Systemic safety*

5. vital signs
6. routine clinical chemistry testing (including CRP, IgG, IgM and full/differential blood counts)
7. Immunopathology essays will include specific enzyme-linked immunosorbent assays for humoral antibodies against rAAV8 capsid protein
8. Biodistribution will be monitored by polymerase chain reaction studies on rAAV2/8 genome in blood, urine, saliva and lachrymal fluid.

## 7.2.2. Data Monitoring Committee

A Data Monitoring Committee (DMC) will monitor patients' safety at regular meetings. At crucial steps of the trial (see figure 3) such as after day 30, when safety data of previous patient cohort is available, the committee will provide a go/no go decision for the treatment of the next dose cohort. The DMC consists of [name], Tübingen, [name], Oxford, and [name], Montpellier. The members of the DMC are independent of the clinical trial.

## 7.2.3. Definitions

### Adverse Event (AE)

An AE or adverse experience is any untoward medical occurrence in a patient or clinical investigation participant administered a medicinal product, which does not necessarily have to have a causal relationship with the study treatment.

An AE can therefore be any unfavourable and unintended sign (including an abnormal laboratory finding), symptom or disease temporarily associated with the use of the study medication, whether or not considered related to the study medication.

### Adverse Reaction (AR)

An AR or adverse reaction is an untoward and unintended reaction to a medicinal product related to any dose. The phrase "reaction to a medicinal product" means that a causal relationship between a study medication and an AE is at least a reasonable possibility, i.e., the relationship cannot be ruled out. All cases judged by either the reporting medically qualified professional or the sponsor as having a reasonable suspected causal relationship to the study medication qualify as adverse reactions.

### Serious Adverse Event (SAE)

A serious adverse event is any untoward medical occurrence that at any dose:

- Results in death,
- Is life-threatening,
- Requires inpatient hospitalization or prolongation of existing hospitalization,
- Results in persistent or significant disability/incapacity, or
- Is a congenital anomaly/birth defect.

It is important to consider that the term "life-threatening" in the definition of "serious" refers to an event in which the participant was at risk of death at the time of the event; it does not refer to an event, which hypothetically might have caused death if it were more severe.

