### Expected Serious Adverse Events/Reactions

Expected serious adverse events/reactions (ESAE/ESAR) are most likely to be related to (1) complications of retinal surgery, (2) immune reactions to the vector capsid or (3) immune reactions and/or toxic effects on retinal function caused by expression of human CNGA3 protein.

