#### *(1) Complications of retinal surgery*

There are known complications of three port pars plana vitrectomy and subretinal surgery. These include retinal detachment, traumatic cataract, suprachoroidal and/or subretinal hemorrhage and endophthalmitis.

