#### *(3) Immune reactions and/or toxic effects on retinal function caused by AAV8-CNGA3*

Due to the time required for transgene expression following subretinal delivery of AAV8, it is unlikely that any toxic effects of the transgene product would be evident prior to at least two weeks after surgery at the earliest. These might include similar immune reactions as described in (2) above. Also any toxic effects of AAV8-CNGA3 on visual function might be manifest by a worsening of visual acuity after the initial period of post-operative recovery. Potential toxic effects on retinal function are likely to be manifest as a significant drop in visual acuity (defined by 15 letters or more).

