### 7.3. Reporting Procedures for all Adverse Events

All AEs occurring during the study observed by the investigator or reported by the participant, whether or not attributed to study medication, will be recorded on the CRF. The following information will be recorded: description, date of onset and end date, severity, assessment of relatedness to study medication, action taken and the outcome of AEs.

AEs considered related to the study medication as judged by a medically qualified investigator or the sponsor will be followed until resolution or the event is considered stable and/or until the end of the follow-up period (4 years).

The severity of events will be assessed on the following scale: 1 = mild, 2 = moderate, 3 = severe. The relationship of AEs to the study medication will be assessed by a medically qualified investigator and discussed with the PI.

[figure not shown]

Any *pregnancy* occurring during the clinical study and the outcome of the pregnancy of female patients or fathered by trial participants, should be recorded and followed up for congenital abnormality or birth defect until delivery. Pregnancy itself is documented as AE, in case of hospitalization as SAE.

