### 7.3.1. Reporting Procedures for Serious Adverse Events

The Data Monitoring Committee (DMC) will review all SAEs for the study at certain time-points of the trial. The DMC is detailed in Appendix B and may hold personal /TC/electronic meetings. The DMC will meet at regular intervals and consider:

- Occurrence and nature of adverse events
- Whether additional information on adverse events is required
- Consider taking appropriate action where necessary to halt the trial (see below)
- Act / advise on incidents occurring between meetings that require rapid assessment (e.g. SUSARs)

Especially before the second and third trial cohort, when the Day 30 results for each patient are available, the DMC must meet and make a go/no-go decision for the treatment of the next dose cohort, which needs to be reported to the PI as soon as possible.

All SAEs will be reported to the DMC within one day of discovery or notification of the event. All SAE information will be recorded on an SAE form, which will be sent electronically to members of the DMC. Additional information received for a case (follow-up or corrections to the original case) will be detailed on a new SAE form.

The CRO will – on behalf of the Sponsor - report all AEs, SAEs and SUSARs to the Ethics Committee and the Regulatory Authority (PEI) in an annual safety report. Fatal or life-threatening SUSARs will be reported within 7 days and all other SUSARs within 15 days. The PI will also inform all members of the study group on all adverse events that might affect the safety of participants.

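### The SAE definition has no sight-threatening or important-medical-event criterion and no link to the protocol's own ocular safety events, and the pregnancy rule makes an uncomplicated hospital delivery an SAE

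*Supplement*

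**What the plan says.** All references are to protocol version 5.0. Section 7.2.3 calls an untoward medical occurrence serious if it meets any one of five criteria. The first two are death and threat to life; a note narrows the latter, saying that it "refers to an event in which the participant was at risk of death at the time of the event". The third is that the event "Requires inpatient hospitalization or prolongation of existing hospitalization". The fourth reads "Results in persistent or significant disability/incapacity, or" and leads on to the fifth, a congenital anomaly.

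The same section then describes expected serious events: "Expected serious adverse events/reactions (ESAE/ESAR) are most likely to be related to (1) complications of retinal surgery", followed by immune reactions to the capsid and immune or toxic effects of the transgene. On surgical complications it says: "These include retinal detachment, traumatic cataract, suprachoroidal and/or subretinal hemorrhage and endophthalmitis". The capsid paragraph mentions severe intraocular inflammation. The transgene paragraph mentions a fall in acuity of 15 letters or more.

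Section 7.2.1 lists two ocular safety events under the primary endpoint: a loss of at least 15 letters, and severe vector-induced inflammation that does not respond to treatment.

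On escalation, 7.3.1 says: "All SAEs will be reported to the DMC within one day of discovery or notification of the event". On pregnancy, 7.3 says: "Pregnancy itself is documented as AE, in case of hospitalization as SAE".

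**The concern.** In a first-in-human subretinal trial, the events of most interest are those that threaten sight. They seldom threaten life and may be handled without admission. The five criteria do not mention them, and nothing says how the 15-letter threshold, used in both 7.2.1 and 7.2.3, relates to seriousness. Two investigators could class the same event differently, each with support from the text.

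The label matters because only an SAE carries one-day notice to the DMC, and only a serious reaction can be a SUSAR, which is the third stop rule in 7.4 and triggers reporting within 7 or 15 days. Section 10.4 also tabulates SAEs beside AEs.

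The pregnancy sentence errs the other way: it gives SAE status to an ordinary hospital birth, which is not an untoward event.

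**Working it through.** No figure in the plan is at issue, so the check is mainly a comparison of passages.

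**1. Events scored against the five criteria**

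- Loss of 15 letters or more in the treated eye, found at D30, patient not admitted: not death, not risk of death, no admission, no anomaly. It is an SAE only if someone judges it a persistent or significant disability.
- Severe inflammation during the three-day stay planned for every patient (7.5) that does not prolong that stay: the same result.
- Cataract or retinal detachment managed without admission: the same result.
- Uncomplicated hospital delivery: an SAE under 7.3. Under 7.2.3 it is not untoward, so it is neither an AE nor an SAE. The two sections conflict. The paragraph in 7.3 also covers pregnancies fathered by participants.

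In the first three cases everything rests on the disability criterion, which the protocol does not define for vision. Only the worse eye is treated (Synopsis), so the judgement is not obvious.

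**2. What depends on SAE status**

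- Dependent: one-day DMC notice (7.3.1), SUSAR status (7.2.3, 7.4) and the SAE table (10.4).
- Not dependent: recording as an AE (7.3), the ocular safety events (7.2.1), the first two stop rules (7.4), and the DMC's remit to consider adverse events in general (7.3.1).

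**3. Why one-day notice matters within a cohort**

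Section 3.1 keeps four weeks between injections, and the required DMC meeting follows the Day 30 data of all three patients. Assume intervals of exactly 28 days.

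- Patient 1's D14 visit (± 3 days) falls on days 11 to 17, which is 28 − 17 = 11 to 28 − 11 = 17 days before patient 2's injection.
- Patient 3 is injected on day 2 × 28 = 56, and the nominal D30 visit is day 56 + 30 = 86.
- From patient 1's D14 visit to the last D30 visit is 86 − 14 = 72 days.

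An event found at D14 and not classed as serious therefore has no prescribed one-day route to the DMC before patient 2 is treated. Section 7.3.1 mentions regular meetings, which might come sooner, but gives no interval.

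**4. Scale**

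Table 2 in 7.5 predicts cataract formation in 10–20% and retinal detachment or breaks in 1%. With nine patients:

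- Cataract: 9 × 0.10 = 0.9 to 9 × 0.20 = 1.8 expected; chance of at least one, 1 − 0.9⁹ = 61% to 1 − 0.8⁹ = 87%.
- Detachment or breaks: 9 × 0.01 = 0.09 expected; chance of at least one, 1 − 0.99⁹ = 8.6%.

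These count events that would need classifying, not events misclassified. Table 2 gives cataract formation, whereas 7.2.3 names traumatic cataract. The documents do not give the share managed without admission, prolonged stay or disability, so the number missed lies anywhere from none to all.

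**The case against.** The case against is substantial.

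- A reader might infer that seriousness turns largely on hospital admission. The text does not support that. Admission is one of five alternatives, and the disability criterion asks for persistent or significant disability, so a marked loss can qualify before its persistence is known. The protocol itself calls a 15-letter fall significant in 7.2.3 (3) and 7.5. This stands and limits the gap to events not judged a disability. It does not close the gap, because neither passage equates a significant fall in acuity with a significant disability.
- A reader might also infer that 7.2.3 declares every listed complication serious, so that each non-serious one is a contradiction. It does not. It names likely sources of serious events, speaks of severe vitritis, and introduces capsid reactions as not expected. A mild cataract that is not an SAE contradicts nothing.
- Key events are not lost. AEs and SAEs are both listed and tabulated, the 7.2.1 ocular events stand apart from SAE status, and the first two stop rules do not need it. This also stands. The stop rules are only a partial substitute for prompt notice, though: the first requires more than 15 letters and attribution to the vector, whereas 7.2.1 counts a loss of exactly 15.
- SUSAR status also needs unexpectedness, judged against the Investigator's Brochure, which is not shown. Whether any event would lose that route in practice is therefore not demonstrated.
- A normal birth would be recognisable in a listing of nine patients, and 7.2.3 can be read as overriding 7.3. That makes the pregnancy point minor, but the two sections still disagree.

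**Conclusion.** The concern holds as a gap in wording. The seriousness criteria do not cover sight-threatening or medically important events and are not linked to the protocol's own ocular safety events. An event of that kind without admission, a longer stay or a judgement of disability need not be an SAE. What is then exposed is the one-day notice to the DMC, possible SUSAR status and the AE or SAE label. Recording of the event, the 7.2.1 endpoints and the two ocular stop rules are unaffected.

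The number of events affected cannot be computed. The 61–87% chance of at least one cataract might be read as the chance of a missed SAE; it is not, and it also assumes that Table 2's rate applies to the cataract named in 7.2.3. The documents give no pregnancy rate, so the number of births labelled SAE cannot be stated either. The pregnancy sentence is a separate, smaller inconsistency between 7.3 and 7.2.3.

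**What to change.** In 7.2.3, add a seriousness criterion for any event that the investigator judges sight-threatening in either eye. State that the two ocular safety events in 7.2.1, a loss of 15 letters or more and severe vector-induced inflammation unresponsive to treatment, always meet it, whether or not the patient is admitted. State also that the other complications named under 7.2.3 (1) to (3) count only when judged sight-threatening or when they meet another criterion. A blanket rule making every listed complication serious would go too far, since it would include a minor cataract.

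In 7.3, reconcile the pregnancy sentence with 7.2.3, so that admission for an uncomplicated delivery is not by itself an SAE.

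The cost is protocol wording, a few more SAE forms and a possibly slightly higher SAE count. No dose, treatment or stop rule changes.

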### Serious Adverse Reaction (SAR)

A SAR, a serious adverse reaction, is an adverse event (expected or unexpected) that is both serious and, in the opinion of the reporting investigator, believed with reasonable probability to be due to one of the study treatments, based on the information provided.

### Expected Serious Adverse Events/Reactions

Expected serious adverse events/reactions (ESAE/ESAR) are most likely to be related to (1) complications of retinal surgery, (2) immune reactions to the vector capsid or (3) immune reactions and/or toxic effects on retinal function caused by expression of human CNGA3 protein.

#### *(1) Complications of retinal surgery*

There are known complications of three port pars plana vitrectomy and subretinal surgery. These include retinal detachment, traumatic cataract, suprachoroidal and/or subretinal hemorrhage and endophthalmitis.

#### *(2) Immune reactions to vector capsid*

These are not expected, given the safety history with much larger doses of this vector in non-ophthalmological clinical trials (Nathwani et al., 2011), but cannot be ruled out completely. Therefore, presence of immune reactions will be investigated during the follow-up clinical examinations. Severe immune reactions triggered by the vector are likely to be evident within the first day of administration and might include non-infectious severe vitritis, chorioiditis or endophthalmitis. There may be additional systemic reactions such as headache and fever. Hence the patient will be monitored overnight and undergo a check up on the day after surgery.

#### *(3) Immune reactions and/or toxic effects on retinal function caused by AAV8-CNGA3*

Due to the time required for transgene expression following subretinal delivery of AAV8, it is unlikely that any toxic effects of the transgene product would be evident prior to at least two weeks after surgery at the earliest. These might include similar immune reactions as described in (2) above. Also any toxic effects of AAV8-CNGA3 on visual function might be manifest by a worsening of visual acuity after the initial period of post-operative recovery. Potential toxic effects on retinal function are likely to be manifest as a significant drop in visual acuity (defined by 15 letters or more).

### Suspected Unexpected Serious Adverse Reaction (SUSAR)

A suspected unexpected serious adverse reaction is a reaction, the nature or severity of which is not consistent with the applicable product information as documented in the Investigator's Brochure and which at the same time is regarded as potentially related to the administration of the investigational product.

### 7.3. Reporting Procedures for all Adverse Events

All AEs occurring during the study observed by the investigator or reported by the participant, whether or not attributed to study medication, will be recorded on the CRF. The following information will be recorded: description, date of onset and end date, severity, assessment of relatedness to study medication, action taken and the outcome of AEs.

AEs considered related to the study medication as judged by a medically qualified investigator or the sponsor will be followed until resolution or the event is considered stable and/or until the end of the follow-up period (4 years).

The severity of events will be assessed on the following scale: 1 = mild, 2 = moderate, 3 = severe. The relationship of AEs to the study medication will be assessed by a medically qualified investigator and discussed with the PI.

[figure not shown]

Any *pregnancy* occurring during the clinical study and the outcome of the pregnancy of female patients or fathered by trial participants, should be recorded and followed up for congenital abnormality or birth defect until delivery. Pregnancy itself is documented as AE, in case of hospitalization as SAE.

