Nevertheless, all patients in this trial will be screened regularly even after study close out.

Subjects will be encouraged to monitor themselves and to assist in reporting adverse events; they will be provided with laminated wallet-sized cards with investigator contact information. Additionally, health care professionals treating the study patients, who are not otherwise associated with the clinical trial, will be notified to provide prompt reports of adverse events to the investigators. Investigators will maintain in the case history records of exposures to mutagenic agents and other medicinal products along with subjects' adverse event profiles. Clinical information will focus on information pertaining to new malignancies, new incidence or exacerbation of a pre-existing neurological disorder, new incidence or exacerbation of a prior rheumatologic or other autoimmune disorder, and new incidence of a hematologic disorder. For the subsequent years, subjects will be contacted at a minimum of once per year. A clinical questionnaire, administered by telephone call or at the eye hospital Tübingen or at the subject's home ophthalmological treatment centre, will focus on information pertaining to new malignancies, new incidence or exacerbation of a pre-existing neurological disorder, and new incidence or exacerbation of visual disturbances. It will ask subjects to describe any adverse events, including any unexpected illness and/or hospitalization, and provide a description of exposures to mutagenic agents and other medicinal products.

Dissemination of rAAV.hCNGA3 would most likely only occur between human beings, since it is derived from AAV2/8. However no replication is expected in normal cells of treated individuals exposed to the replication-deficient virus, or from exposure of uninfected people to treated individuals.

**Germline transmission** is theoretically possible but requires biodistribution far beyond what could be detected today combined with the extremely unlikely event of genomic integration.

Currently, there is no experience with the specific **teratogenicity** of the rAAV.hCNGA3 vector, therefore the risk for an unborn child in case of an unforeseen conception, especially during the first half of the study participation, cannot be judged.

Generally, there is the potential of no subjective or objective benefit despite the risks of the procedure.

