#### 8.4.34. Adverse event (AE) recording

Open questions regarding changes in health status since last visit are asked by the study physician at the beginning of each study visit.

[figure not shown]

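### Section 7.3 stops following pregnancies for birth defects at delivery, and no later planned contact in the protocol text asks specifically about the child

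*Supplement*

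**What the plan says.** Section 7.3 covers pregnancies of female patients and those fathered by participants. The pregnancy and its outcome are to be "recorded and followed up for congenital abnormality or birth defect until delivery". The pregnancy itself is an AE, or an SAE if there is hospitalization. No time point after delivery is given.

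Section 7.2.3 defines an AE as "any untoward medical occurrence in a patient or clinical investigation participant administered a medicinal product". Among the seriousness criteria for an SAE it lists: "Is a congenital anomaly/birth defect".

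After treatment, contacts run to D365, then M24, M36, M48 and M60. Sections 3.2 and 7.5 add a yearly contact after that. At each study visit, section 8.4.34 provides: "Open questions regarding changes in health status since last visit are asked by the study physician". Section 7.5 describes the yearly questionnaire as focusing on new malignancies, "new incidence or exacerbation of a pre-existing neurological disorder, and new incidence or exacerbation of visual disturbances". It also asks about the subject's adverse events and about exposures.

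On the risk itself, section 7.5 states that "the risk for an unborn child in case of an unforeseen conception, especially during the first half of the study participation, cannot be judged". Section 11 adds that no germline data have been published from other ocular gene therapy studies.

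**The concern.** Some congenital anomalies are not apparent at birth. The plan actively looks for birth defects up to delivery and then has no child-specific question, although it goes on seeing or calling the parent for years. In a first-in-human gene therapy trial whose own risk section calls the risk to an unborn child unknown, a pregnancy would be a rare source of information on that question. A late-recognised anomaly could be missed because a parent asked about his or her own health need not think to mention the child.

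**Working it through.** The plan gives no figure to reproduce. The check has two parts: what the later contacts ask, and when a child-specific question would fall.

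**1. Where a finding after birth could enter**

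| Route | Scheduled? | Names the child? |
|---|---|---|
| Pregnancy follow-up (7.3) | Yes, ends at delivery | Yes |
| Open AE question at visits to M60 (8.4.34) | Yes | No, concerns health status since last visit |
| Yearly questionnaire (7.5) | Yes | No, as described |
| Visit lists and flowchart, D365 and M24 to M60 | Yes | No |
| SAE criterion for congenital anomaly (7.2.3, 7.3.1) | No, applies once reported | By implication |
| Follow-up of related AEs to the end of the 4 years (7.3) | Applies once reported and judged related | No |
| Self-report and reports from professionals treating the participant (7.5) | No | No |

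The pregnancy outcome is recorded, so a defect seen at birth is captured. Every route after birth is either a generic prompt or a spontaneous report. A child-specific question is what is missing.

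**2. Timing of one added question**

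From the documents: contacts at D365 (±14 days) and M24 to M60 (±1 month), then yearly; contraception for four months after injection. With a month of 30.4375 days, four months is 121.75 days, taken as days 0 to 122. M24 is day 730.5 and M60 is day 1826.25.

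Assumed, not in the documents: birth 245 to 280 days after conception, and a six-month minimum of 6 × 30.4375 = 182.6 days.

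*Why a minimum interval is needed.* If the question were put at the first contact after birth, it could fall on the day of birth: 120 + 245 = 99 + 266 = 85 + 280 = 365. At 245 days' gestation the wait to D365 is 120 − c for conception day c. This is under 30 days for c = 91 to 120, which is 30 of the 123 conception days. The count is also 30 at 266 days (c = 70 to 99) and at 280 days (c = 56 to 85).

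*Conception inside the contraception period.* Birth falls between day 0 + 245 = 245 and day 122 + 280 = 402. D365 is at most 365 − 245 = 120 days after birth, so it never meets the minimum. M24 always does: it falls 730.5 − 402 = 328.5 to 730.5 − 245 = 485.5 days after birth, about 11 to 16 months. With the one-month window the range is 298 to 516 days.

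*Conception in months 4 to 12.* With gestation of about 9 months, birth is at about month 13 to 21. The qualifying contact is M24 for births up to month 24 − 6 = 18, and M36 after that.

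*Any birth up to M60.* The longest nominal wait is 182.6 + 365.25 = 548 days, or 18 months. With windows up to M60 it is 548 + 2 × 30.44 = 609 days, or 20 months. Births after day 1826.25 − 182.6 = 1644 (month 54) need a yearly contact after M60.

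*Early discontinuation.* Section 7.4 caps follow-up at one year after termination. If termination is on day d and birth on day b, the minimum can be met only if d + 365 ≥ b + 182.6. For b = 245 this needs d ≥ 62.6, and for b = 402 it needs d ≥ 219.6. Earlier terminations may not allow six months, so the rule needs a fallback to the last follow-up contact.

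**The case against.** A reader might infer that a defect found after delivery is lost, or enters the data only if someone volunteers it. The documents do not support that. The study physician asks an open question at every visit to M60, and the yearly questionnaire asks for any adverse events. These are scheduled prompts, even if generic. Congenital anomaly is an SAE criterion, and SAEs go to the DMC within one day of discovery or notification, with no cut-off at delivery. Section 7.3.1 also says: "Additional information received for a case (follow-up or corrections to the original case) will be detailed on a new SAE form". Health professionals treating the participants "will be notified to provide prompt reports of adverse events to the investigators", although these are the participant's clinicians and not necessarily the child's. An anomaly judged related could be followed to the end of the 4-year follow-up. So 7.3 ends active pursuit, not reporting.

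A second tempting inference is that the protocol shows a danger to offspring. It does not. It calls germline transmission theoretically possible but dependent on biodistribution far beyond what can be detected. It reports no vector DNA in blood at 72 hours in 12 primates injected subretinally (six per dose). It also says that, in the trials it cites, non-intravenous routes left no vector genome in semen after Day 7. This evidence is indirect, but it is the basis of the four-month rule.

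Third, the questionnaire form, CRF, Procedure Manual, consent pages and the CRO's procedures are not shown and may contain a pregnancy follow-up item. The point is therefore confined to the protocol text.

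These objections reduce the size of the gap. They do not supply a question about the child at any planned contact.

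**Conclusion.** The point holds as a modest gap in planned safety ascertainment. Pursuit of birth defects ends at delivery, and the later contacts described in the protocol rely on generic prompts or spontaneous reports. The effect is small: nine adults, pregnancy tests at entry and up to D365, four months of required contraception, and no bearing on any endpoint, dose decision or planned analysis. The documents allow no estimate of how likely a pregnancy or a late-recognised anomaly is, and none is offered. The wording of 7.3 is certain. Whether there is a gap in practice depends on documents not shown. The timing results rest on the assumed gestation and the assumed six-month minimum; no section of the protocol sets a postnatal standard. One well-timed question is enough, and asking at every contact to M60 would go further than the problem needs. The change is worth making because the protocol itself calls the risk unknown and the contacts already exist.

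**What to change.** In section 7.3, replace the end point at delivery with: *at delivery and at the first planned study contact at least 6 months after birth (M24 to M60, the yearly contact in 3.2 and 7.5, or, after early discontinuation, the last follow-up contact); any anomaly reported is documented on the SAE form under 7.3.1.* State in the protocol that six months is a chosen minimum.

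No visit or test is added, only one question to the participant. Where the pregnancy is a partner's, permission must cover the question. Section 13 requires approval of an amendment by the PEI and the ethics committee, and revised patient information signed by all patients. After a very early discontinuation the last follow-up contact may come less than six months after birth, or before it; the fallback accepts this.
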